### Statistical analysis

As the intervention is conducted in males and females separately, data will be initially analyzed in males and females separately. We will first compare the groups in baseline demographics, socioeconomic and clinical characteristics, and missing values. To follow the CONSORT guidelines for reporting RCTs [42] we will perform both complete case and intent-to-treat (ITT) analyses to allow readers to interpret the effect of the intervention. In ITT analysis, we will include all participants with the group status they are originally assigned. Following the recommendations published in the N Engl J Med [43], and BMJ [44], missing values will be imputed using multiple imputation with 20 imputed datasets.

The proportions of MDE at 12 months (primary objective) and at 3 months will be estimated and compared between the intervention and control groups. For the primary objective, mixed-effects logistic regression modeling will be performed using combined imputed datasets based on Rubin’s rules, adjusting for the effects of demographic and socioeconomic characteristics, baseline PHQ-9 score, predicted risk of MDE, caregiving burden, and comorbid physical conditions [45]. Additionally, it will account for within-participant correlation over time through the incorporation of random effects. Within-and between‐group effect sizes will be estimated by computing Cohen’s h [46]. The analyses will be repeated among complete cases. Sensitivity analyses (best-worst and worst-best) will be conducted under the assumption of missing not at random [43, 44]. The PHQ-9 mean scores at 3- and 12-months, the changes in SSSU scores and the proportions of mental health service use in the past year between the groups will be compared using t test and Chi square test, respectively (secondary objective #1 & #2). We will investigate if self-efficacy is a moderator in the relationships between the intervention and outcomes by including a two-way interaction term between self-efficacy and intervention status in the models (secondary objective #3). If no evidence supports moderation by self-efficacy, we will examine if self-efficacy plays a role of mediator using structural equation modeling.

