### Sample size calculation

In our 2020/21 pilot study, recruitment and intervention was conducted in male and female participants, separately. Participants were assessed at baseline and 3 months post intervention. Comparing the proportions of moderate/severe MDE (having a PHQ-9 score of 15+) (31) between baseline and 3-months, the proportion of MDE in the male intervention group reduced from 15.7 to 6.2% (-9.5%), whereas the proportion in the male control group increased from 10.8 to 12.7% (+ 1.9%). The proportion in the female intervention group changed from 12.8 to 14.5% (+ 1.7%), whereas the proportion in the female control group increased from 7.4 to 17.1% (+ 9.7%). However, the increase in depressive symptoms in female intervention group (1.9%) was not statistically significant. The slight increase may be due to the fact that the pilot was conducted during the height of COVID-19 when females were more emotionally affected [47, 48]. It does not mean that the intervention is harmful as compared to the increase in the control group; it may be an indication that the intervention helped maintain the mental health of females during the pandemic, whereas the mental health of those in the control group deteriorated significantly. In the post pandemic era, we expect that females who are in the intervention group will have a lower risk of MDE than those in the control group.

Assuming the 12-month incidence of MDE in female intervention and control groups is 1.7% and 9.7%, respectively, α = 0.05 and β = 0.80, G*Power calculation [49] indicates that at least 262 female participants are needed at baseline (131 in each group). Assuming the response rate over 12 months is 80% as we achieved in our previous trial [33], 330 female participants should be recruited. We also plan to examine the moderation effect by self-efficacy. Therefore, we proposed to recruit 500 male and 500 female participants at baseline which will results in the power of 82% for the moderation analysis based on 50 Monte Carlo simulations.

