We acknowledge concerns about the changes in response rates in telephone surveys due to cell phone use and telemarketing. Including eligible participants across the country will enhance the generalizability of the study. Given the vast geographic area of Canada, RDD is the only feasible method. The goal of this study is to recruit participants for a RCT, rather than selecting a representative sample. In an RCT, selection bias is not a serious concern as long as the bias is the same across the intervention and control groups [24]. To mitigate the risk, the telephone survey firm will also access the validated cellphone database. However, the use of cellphone numbers is associated with increased costs. Another potential risk of the proposed study is attrition which may incur selection bias. In previous RCT trial, the response rate at 12-month was 80% in females and 77% in males [33]. As we plan to use the same recruitment and follow-up methods, we anticipate the same response rate in the proposed RCT. Our strategies for reducing attrition will include appropriately designed introductory scripts, a minimum of nine call back attempts spaced over weekdays and times of day and provision of a $25 incentive for each completed interview.

*Knowledge translation (KT).* KT will be in the form of peer reviewed publications, conference presentations and research website dissemination. Only aggregated data will be presented. If the results of this study support the hypothesis, our goal is to implement the coach-guided PDRC in the community as a selective prevention program at Tier 1 and 2 levels through knowledge dissemination and collaboration with key knowledge users, including Public Health Agency of Canada, Mental Health Commission of Canada, Canadian Mental Health Association and mental health units of health regions. We will publish the results of the study in peer-reviewed journals, present at academic and non-academic conferences and symposia, and disseminate the key findings through social media. The authorship of the publications generated from this trial will be determined according to the BMC Medical Research Methodology authorship guidelines. No scientific writers will be used.

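### At the loss and event rates the protocol expects, its only named missing-not-at-random analysis gives opposite significant extremes with or without an effect, so it cannot separate a robust from a fragile primary result

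*Protocol article*

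**What the plan says.** The Statistical analysis section of the protocol article plans three treatments of missing data.

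- Main analysis: "missing values will be imputed using multiple imputation with 20 imputed datasets", combined by Rubin's rules in a mixed-effects logistic model for MDE.
- Second analysis: "The analyses will be repeated among complete cases".
- Missing not at random: "Sensitivity analyses (best-worst and worst-best) will be conducted under the assumption of missing not at random".

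The third is the only one that lets non-response depend on the unseen outcome. No graded or tipping-point analysis is named, and no rule says how the extremes would affect the conclusion.

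On the amount of missing data, the Discussion reports that in the previous trial "the response rate at 12-month was 80% in females and 77% in males" and expects the same here. The Sample size calculation uses the same 80%: "Assuming the response rate over 12 months is 80% as we achieved in our previous trial". The only 12-month event rates assumed are for females: "Assuming the 12-month incidence of MDE in female intervention and control groups is 1.7% and 9.7%, respectively".

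**The concern.** A best-worst analysis gives MDE to every missing person in one arm and to nobody missing in the other, then swaps the arms. It is informative when the missing fraction is small relative to the effect. Here the expected missing fraction (20% to 23%) is at least twice the assumed control risk (9.7%) and far above the assumed effect (8.0 points), so the filled-in values dominate the observed ones.

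The Discussion itself names attrition as a possible source of selection bias. The outcome is depression and follow-up is by telephone interview, so people who become depressed could plausibly be harder to reach. A useful sensitivity analysis would show how strong that dependence has to be before the primary result changes. If the planned analysis gives the same answer for a success and for a null trial, readers cannot learn this from it.

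**Working it through.** **Inputs.** Assumed 12-month MDE risks: pI = 1.7% and pC = 9.7% (Sample size calculation, females). Loss d = 20% in females and 23% in males (Discussion). 500 per sex, randomized 1:1, so 250 per arm within each sex. Assumptions added here: equal loss in the two arms; a crude risk difference stands in for the mixed model; filled-in values are treated as observed.

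**The plan's own figure.** The protocol states "α = 0.05 and β = 0.80"; the second value is read as power. With pooled risk 0.057 and a two-sided test without continuity correction:

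n = [1.96 × √(2 × 0.057 × 0.943) + 0.842 × √(0.017 × 0.983 + 0.097 × 0.903)]² / 0.08² ≈ 131 per arm.

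This matches the stated 131 per arm (262 in all). Dividing 262 by 0.80 gives 328, against 330 stated. The inputs are therefore being read as the authors used them.

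**Extremes under the full assumed effect, d = 20%, 250 per arm.**

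- Worst case for the intervention: 0.8 × 1.7% + 20% = 21.4%, against 0.8 × 9.7% = 7.8%. Difference +13.6 points (95% CI 7.5 to 19.7). Pooled risk 14.6%, standard error √(0.146 × 0.854 × 2/250) = 0.0316, z = 0.136/0.0316 ≈ 4.3 towards harm.
- Best case: 0.8 × 1.7% = 1.4%, against 0.8 × 9.7% + 20% = 27.8%. Difference -26.4 points (-32.1 to -20.7).

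**Extremes under no effect (illustrative 10% in both arms), d = 20%.** 28.0% against 8.0% in one direction and the reverse in the other: +20.0 points (13.5 to 26.5) and -20.0 points (-26.5 to -13.5). Both are significant.

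**Other scenarios.**

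| Scenario | Worst case for intervention | Best case |
|---|---|---|
| 23% loss, 1.7% vs 9.7% (female rates applied to males, an assumption) | +16.8 (10.6 to 23.1) | -29.2 (-35.0 to -23.3) |
| 23% loss, male pilot 3-month proportions, 6.2% vs 12.7% | +18.0 (11.3 to 24.7) | -28.0 (-34.4 to -21.6) |
| Sexes pooled, 500 per arm, 21.5% loss, 1.7% vs 9.7% | +15.2 (10.9 to 19.6) | -27.8 (-31.9 to -23.7) |

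Pooling the sexes does not help, because the sign depends on the missing fraction and not on the sample size.

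**What would survive.** The worst case keeps its sign only if (1 - d)pI + d < (1 - d)pC, that is, pC - pI > d/(1 - d).

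- d = 20%: 0.20/0.80 = 25.0 points.
- d = 23%: 0.23/0.77 = 29.9 points.

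Both exceed the entire assumed control risk of 9.7%. Even zero MDE among observed intervention participants would become 20.0% against 7.8%. Conversely, an 8-point effect keeps its sign only if d is below 0.08/1.08 = 7.4%, and at 250 per arm it stays significant only up to about 3% loss.

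**What a graded analysis would show.** Take the design effect, 20% loss, and missing controls kept at 9.7%. Let q be the MDE risk among missing intervention participants.

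- Significance is lost near q = 19%: 0.8 × 1.7% + 0.2 × 19% = 5.2% against 9.7%, difference -4.5 points, upper limit just above zero. The odds multiplier is (0.19/0.81)/(0.017/0.983) ≈ 13.6.
- The difference reaches zero at q = (9.7% - 0.8 × 1.7%)/0.2 ≈ 42%.
- At 23% loss the two thresholds are about 17% and 36%.
- A narrow grid would miss both. Multiplying the odds by 4 gives q ≈ 6.5%, hence 2.7% against 9.7%, z ≈ 3.3, still clearly significant.

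Allowing for imputation uncertainty would widen the intervals, so the loss of significance would come somewhat earlier than shown.

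**The case against.** The strongest reply is that nothing stated is wrong. Best-worst and worst-best bounds are a recognised method, are labelled as sensitivity analyses, and sit beside multiple imputation and a complete-case repeat. Wide bounds honestly show what 20% to 23% loss allows when nothing is assumed. The article is condensed, and a statistical analysis plan that is not shown may add a graded analysis.

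Much of this stands. The bounds are valid, and the absence of tipping-point detail from an article would not by itself be a finding. But the protocol does name its approach to data missing not at random, and that approach can be tested against the protocol's own rates. There it fails to discriminate. The complete-case repeat does not fill the gap, since it does not model dependence of non-response on the unseen outcome.

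A reader might infer that the planned check would overturn any positive finding. The protocol does not support that: it attaches no decision rule to the extremes, and the primary conclusion rests on the multiply imputed model. A reader might also infer that the extremes are uninformative whatever happens. That holds at the expected loss and event rates; with loss of a few per cent they would be informative.

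**Conclusion.** The point holds as a weakness in a stated sensitivity analysis, not as an error in the primary estimate. At 20% loss the extremes run from -26.4 to +13.6 points under the full assumed effect and from -20 to +20 points under none, with significant results in both directions each time. An observed difference above 25 points (about 30 at 23% loss) would be needed to keep its sign, which the assumed control risk of 9.7% rules out.

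This rests on equal loss by arm, on response rates like those of the previous trial, and on 12-month event rates that the protocol states for females only. The male pilot proportions lead to the same conclusion. The protocol should be improved here; the extremes need not be removed.

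**What to change.** Make delta-adjusted multiple imputation the main missing-not-at-random sensitivity analysis of the primary outcome. Shift the imputed MDE risk of non-responders, vary the shift separately by arm, and report the tipping point at which the primary conclusion changes. Keep best-worst and worst-best as descriptive outer bounds.

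Set the grid in advance and extend it until the conclusion changes, or define it directly by the MDE risk among non-responders. Do not cap the odds multiplier at a small value such as 4: at the design effect such a grid never reaches the tipping point and would always report robustness.

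The cost is small. The 20 imputed datasets are already planned, so the work is a shift applied to them, a little more reporting, and a grid that has to be chosen before the data are seen.

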#### Screening

Once a potentially eligible participant is identified, the interviewer will confirm the participant’s age and administer the lifetime version of the Composite International Diagnostic Interview – Major Depression (CIDI) [36] MDE module and the sex-specific MVRPs to assess eligibility. Interviewees who have a MDE in the past 2 months or are below the risk thresholds based on the MVRPs, will be excluded. Individuals with an ongoing MDE will be encouraged to contact their family doctors and information about local mental health resources will be provided. For those who are at low risk, the website of the MVRPs will be provided so they may monitor their risk in the future.

*Baseline assessment* will include demographic and socioeconomic status, depressive and anxiety symptoms, physical illness, self-help behaviours, mental health services use and self-efficacy.

*Randomization* will be carried out immediately after baseline assessment, in male and in female participants separately because the MVRPs are sex-specific and the thresholds of high-risk differ by sex. Most survey firms use a survey software containing a random number generator which randomly creates a digit. This randomization approached was used in our previous RCT, and the intervention and control groups of the trial were balanced in baseline characteristics [33].

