As part of sex-/gender-based analysis, when analyzing the data by biological sex, we will first describe gender identity and the gender role related variables (employment status, education, income levels, and caregiving burden) to identify any gender differences and intersectionality (overlapping and interdependence among the gender role related factors) within and between the groups. In sex specific analysis, we will control the effects of gender and gender role related variables in the models. Additionally, we will evaluate the impact of the intervention on the risk of MDE by gender through stratified analysis and logistic regression modeling. As exploratory analyses, we will compare the outcomes between groups in completers, by history of MDE, and by gender identity.

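### The t tests planned for PHQ-9 and self-help scores are valid but lose precision by not adjusting for the baseline scores the trial already collects

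*Protocol article*

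**What the plan says.** In the protocol article, Statistical analysis, the continuous secondary outcomes are "The PHQ-9 mean scores at 3- and 12-months, the changes in SSSU scores" (the second being the SSUS of the outcomes section). Together with service-use proportions, these "between the groups will be compared using t test and Chi square test, respectively". So PHQ-9 is tested as a raw follow-up mean, self-help as a change score, and service use by an unadjusted chi-square.

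The baseline values exist. Under Screening, the baseline assessment covers "depressive and anxiety symptoms, physical illness, self-help behaviours, mental health services use and self-efficacy".

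The same Statistical analysis section fits the primary MDE model "adjusting for the effects of demographic and socioeconomic characteristics, baseline PHQ-9 score, predicted risk of MDE" and further covariates, but says this for the primary objective only. It also says that "data will be initially analyzed in males and females separately", and later adds: "In sex specific analysis, we will control the effects of gender and gender role related variables in the models". Neither statement brings the baseline value of PHQ-9 or SSUS into the analysis of that outcome.

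**The concern.** A baseline score is usually one of the strongest predictors of the same score at follow-up. The plan uses baseline PHQ-9 when MDE is the outcome but not when PHQ-9 itself is. It also handles two scale scores in two ways without giving a reason: one ignores baseline, the other subtracts it in full.

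At stake are the answers to the secondary questions on self-help behaviour and depressive symptoms. Both would carry more variance than the data require. A chance baseline difference would pass in part into the PHQ-9 contrast and, with the opposite sign, into the SSUS change contrast. The sexes are analysed separately first, so the working sample is 500 per sex rather than 1,000, and the lost precision matters more.

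This is not a detail left to an unseen analysis plan: the protocol article names the tests.

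**Working it through.** **The plan's own figure.** The only sample size given is for the primary outcome in women: 1.7% vs 9.7%, "α = 0.05 and β = 0.80" (0.80 read as power), 131 per group. With the pooled-variance formula, two-sided and without continuity correction, the mean proportion is 0.057 and

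n = [1.96 × √(2 × 0.057 × 0.943) + 0.8416 × √(0.017 × 0.983 + 0.097 × 0.903)]² / 0.080² = (0.6426 + 0.2718)² / 0.0064 ≈ 130.7, so 131.

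The figure reproduces and this point does not touch it. No sample size is given for comparing the arms on PHQ-9 or SSUS.

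**Inputs.** From the documents: 250 per arm within sex (500 per sex, 1:1) and 80% retention at 12 months (77% in men in the previous trial), so about 250 × 0.80 = 200 analysed per arm. Assumed, because the documents are silent: baseline-to-follow-up correlation r from 0.2 to 0.7, equal SDs at baseline and follow-up, and, for power only, a true effect of 0.25 SD.

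**Variance relative to the follow-up t test**
- Follow-up t test: 1
- Change score: 2(1 − r)
- ANCOVA: 1 − r²

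Baseline adjustment therefore cuts variance by r² against the follow-up t test and by 1 − (1 + r)/2 = (1 − r)/2 against the change score. Power uses the normal approximation with 200 per arm, two-sided 5%.

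| r | Cut vs follow-up t test | Cut vs change score | Power: t test | Power: change | Power: ANCOVA |
|---|---|---|---|---|---|
| 0.2 | 4% | 40% | 70.5% | 50.7% | 72.3% |
| 0.3 | 9% | 35% | 70.5% | 56.1% | 74.6% |
| 0.4 | 16% | 30% | 70.5% | 62.6% | 77.9% |
| 0.5 | 25% | 25% | 70.5% | 70.5% | 82.3% |
| 0.6 | 36% | 20% | 70.5% | 79.8% | 87.8% |
| 0.7 | 49% | 15% | 70.5% | 89.8% | 93.8% |

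Example at r = 0.2: ANCOVA SE = √(2 × 0.96/200) = 0.098 SD; 0.25/0.098 − 1.96 = 0.59, which gives 72.3%.

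With equal SDs, ANCOVA has the smaller variance for every r strictly between 0 and 1, so the direction does not depend on the range chosen.

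**Unequal SDs.** If the baseline SD is k times the follow-up SD, the change-score variance is 1 + k² − 2kr. For k = 0.8 and r = 0.4, 0.5, 0.6 this is 1.00, 0.84, 0.68 against ANCOVA's 0.84, 0.75, 0.64. The cut falls to 16%, 11% and 6%, from 30%, 25% and 20% with equal SDs.

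**Chance imbalance.** With 250 per arm the SE of a baseline mean difference is √(2/250) = 0.089 SD. A realised difference of 0.1 SD shifts the follow-up t test by 0.1r, which is 0.02 to 0.07 SD over the range. It shifts the change score the other way by 0.1(1 − r), which is 0.08 to 0.03 SD. ANCOVA removes both in expectation.

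**The case against.** The strongest reply is that nothing here is an error. With 1:1 randomisation the t tests and the chi-square are valid, the primary analysis already adjusts for baseline PHQ-9, and only secondary outcomes are concerned. That stands and limits the point to efficiency. A reader might infer inflated type I error or systematic bias; the documents support neither. Bias arises only conditionally on the imbalance that happens to be realised.

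Four narrower objections also stand.

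- **Self-help.** It is tempting to say that imbalance is left uncorrected for both scores. For SSUS that is wrong: the change score subtracts baseline, with weight 1 where r would be right under equal SDs. The outcome is also declared as a change, so the test matches the declaration.
- **Service use.** A reader might extend the precision argument to the chi-square. The 1 − r² result does not carry over to a logistic odds ratio. In a simulation of 400 participants (30% baseline use, assumed log odds ratios of 2.0 for baseline use and 0.5 for treatment), adjustment raised the mean SE of the treatment log odds ratio from 0.210 to 0.236, while power rose from 49% to 58%. The estimate moves to a conditional odds ratio; the interval does not narrow.
- **Pilot.** Baseline PHQ-9 of 15 or more was 12.8% vs 7.4% in women, a gap of 5.4 points, against 17.1 − 14.5 = 2.6 points at 3 months. In men it was 15.7% vs 10.8%. This looks like proof that imbalance will recur, but pilot arm sizes are not given and the measure is a proportion, not the mean. With 250 per arm and about 10% prevalence the SE is √(2 × 0.1 × 0.9/250) = 2.7 points, so a 5.4-point gap would be a 2-SE event. The entry criteria on current MDE and PHQ-9 item 9 should also make such scores less common. The pilot is illustration only.
- **Correlation.** The value of r is unknown and could be low over 12 months in people selected to be free of current MDE. At r = 0.2 the PHQ-9 saving is only 4%.

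What does not stand is the suggestion that another part of the plan already adjusts. The gender and gender-role covariates are not the baseline outcome, and the moderation models name only self-efficacy and its interaction with intervention.

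**Conclusion.** The point holds for PHQ-9 and SSUS as an avoidable loss of precision in secondary analyses. With equal SDs and r between 0.2 and 0.7, adjustment cuts variance by 4 to 49% against the planned PHQ-9 test and by 40 to 15% against the planned SSUS test. The SSUS gain shrinks if baseline scores are less spread than follow-up scores. At r = 0.5, with 200 analysed per arm in one sex and a 0.25 SD effect, power would be 82.3% rather than 70.5% under either planned test. The correlation, the equal SDs and the effect size are assumptions; the absence of baseline adjustment and the availability of the baseline scores are stated in the protocol article. The change should be made, but the trial's primary conclusion does not depend on it.

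**What to change.** Replace the t-test wording for PHQ-9 and SSUS with ANCOVA, or with a linear mixed model that contains the baseline score of the outcome, arm, visit and arm-by-visit. Run it within the planned multiple imputation and within each sex as the plan requires, and put sex in as a covariate in any pooled model. Report adjusted mean differences with 95% CIs at 3 and 12 months. SSUS can remain declared as a change: once baseline is a covariate, change and follow-up score give the same arm contrast.

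Adjusting service use for baseline use is optional. It may raise power, but narrower odds-ratio intervals should not be promised.

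The cost is a revised sentence in the analysis section. No new data, sample size or design change is needed, and it can be settled before group status is linked to the interview data after the 12-month interview.
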